# Supporting Life Adjustment in Patients With Lung Cancer Through a Comprehensive Care Program: Protocol for a Controlled Before-and-After Trial

**DOI:** 10.2196/54707

**Published:** 2024-02-13

**Keywords:** comprehensive care, early intervention, adjustment to cancer, return to work, lung cancer, unmet needs, lung, lungs, pulmonary, respiratory, cancer, oncology, prehabilitation, survivor, survivors, survivorship, education, educational

## Abstract

**Background:**

Lung cancer diagnosis affects an individual’s quality of life as well as physical and emotional functioning. Information on survivorship care tends to be introduced at the end of treatment, but early intervention may affect posttreatment adjustment. However, to the best of our knowledge, no study has explored the effect of early information intervention on the return to work, family, and societal roles of lung cancer survivors.

**Objective:**

We report the study protocol of a comprehensive care prehabilitation intervention designed to facilitate lung cancer survivors’ psychological adjustment after treatment.

**Methods:**

A comprehensive care program was developed based on a literature review and a qualitative study of patients with lung cancer and health professionals. The Lung Cancer Comprehensive Care Program consists of educational videos and follow-up visits by a family medicine physician. To prevent contamination, the control group received routine education, whereas the intervention group received routine care and intervention. Both groups completed questionnaires before surgery (T0) and at 1-month (T1), 6-month (T2), and 1-year (T3) follow-up visits after surgery. The primary outcome was survivors’ psychological adjustment to cancer 6 months after pulmonary resection.

**Results:**

The historical control group (n=441) was recruited from September 8, 2021, to April 20, 2022, and the intervention group (n=350) was recruited from April 22, 2022, to October 17, 2022. All statistical analyses will be performed upon completion of the study.

**Conclusions:**

This study examined the effectiveness of an intervention that provided general and tailored informational support to lung cancer survivors, ranging from before to the end of treatment.

**Trial Registration:**

ClinicalTrials.gov NCT05078918; https://clinicaltrials.gov/ct2/show/NCT05078918

**International Registered Report Identifier (IRRID):**

DERR1-10.2196/54707

## Introduction

Lung cancer remains the leading cause of cancer-related mortality worldwide and is prevalent in Korea [1,2]. However, advancements in screening and treatment have notably improved lung cancer outcomes. For example, the 5-year conditional recurrence-free survival rate of patients with surgically resected non–small cell lung cancer (NSCLC) in Korea increased from 51.5% to 68.5% in those diagnosed in the 1990s and the 2010s, respectively [3]. Consequently, the growing number of lung cancer survivors underscores the urgent need to address posttreatment needs.

Surviving lung cancer can substantially impact the quality of life and emotional health [4-6]. Many survivors adjust over time; however, persistent fear and the expectation of a rapid return to normal posttreatment life are common [7,8]. While initial postdiagnosis support is robust, survivors often encounter a new spectrum of concerns as they transition to life after cancer, including managing lingering symptoms and comorbidities that can affect overall well-being [8-10]. The commonly reported symptoms among lung cancer survivors include fatigue, pain, dyspnea, and impaired pulmonary function [11-13]. They also experience psychological distress and a fear of cancer recurrence [14,15]. Studies have shown that interventions focusing on physical rehabilitation and psychological adaptations can be effective for cancer survivors [16,17]. These interventions address both the physical and emotional challenges faced during the recovery process.

Despite the abundant information and support available after diagnosis, survivors later find themselves having a different set of questions and concerns related to life after cancer [18]. Our prior qualitative study of patients with lung cancer revealed the need for information on the expected trajectories after treatment. The patients expressed a desire for guidance in managing symptoms, stress, exercise, and nutrition to ease their “new normal” lives [19]. Recently, the importance of integrating oncological and supportive care has been increasing [20], as early interventions designed to provide supportive care for patients with cancer are in demand. Based on the findings of our qualitative interview, we hypothesized that an intervention introduced in the early stages of lung cancer treatment can help survivors return to their new normal lives.

Recognizing the critical need for early supportive interventions, we developed the Lung Cancer Comprehensive Care Program (LC^3^P). This program aims to support patients from diagnosis through their adjustment to posttreatment life, encompassing their return to work, family, and societal roles. This study aimed to evaluate the effectiveness of LC^3^P in enhancing psychological adjustment to cancer, with the hypothesis that participants receiving the intervention would demonstrate improved adjustment 6 months after surgery.

## Methods

### Study Setting

We designed a controlled before-and-after trial at the Samsung Comprehensive Cancer Center of the Samsung Medical Center (SMC), a university-affiliated hospital in Seoul, Republic of Korea, to evaluate the impact of LC^3^P compared to routine care. This design was selected to minimize the risk of information contamination between the control and intervention groups. This risk is particularly pertinent to educational interventions, in which the exchange of information between participants can confound outcomes.

### Eligibility Criteria

The inclusion criteria for the study are (1) age 18 years or older at enrollment, (2) diagnosis of stage I, II, or III NSCLC, and (3) a plan to undergo pulmonary resection. Patients with (1) recurrent lung cancer, (2) multiple sites of primary cancer, and (3) a history of other cancers or those who had received active cancer treatment within the past 3 years were excluded. Participants who canceled their pulmonary resection, received a confirmed diagnosis of stage IV lung cancer, or wished to withdraw from the study were excluded. All participants will be required to provide written informed consent before undergoing baseline assessment.

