### Data Collection

The clinical trial procedure and intervention are outlined in Figure 1, with the outcomes assessed at baseline (T0), 1 month (T1), 6 months (T2), and 1 year (T3) postoperatively. Baseline data will be collected before surgery and immediately after enrollment. To enhance participant retention and adherence, individuals in both groups received a small token of appreciation upon completion of each of the 3 postoperative follow-up assessments (T1-T3). For participants who discontinued or deviated from the intervention protocols, the data collected up to the point of departure were included in the intention-to-treat analysis to maintain the robustness of the trial results and minimize the impact of attrition bias. The data obtained from self-administered questionnaires were coded and stored in password-encrypted Microsoft Excel (Microsoft Corp) files on a secure computer server. The specific variables measured at each time point are listed in Figure 2.

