### Statistical Analysis

To assess the effectiveness of LC^3^P, we compared the outcomes between the intervention and control groups at multiple time points. The primary analyses involved independent sample 2-tailed *t* tests for continuous variables and chi-square tests for categorical variables to compare baseline characteristics and outcomes between the 2 groups at each follow-up. To account for repeated measures within participants over time and potential within-subject correlations, a mixed-model repeated-measures analysis was used.

In addition to primary analyses, sensitivity analyses probed the robustness of the trial findings under different assumptions regarding missing data and the effects of protocol adherence on treatment outcomes. This included intention-to-treat and per-protocol analyses. Moreover, subgroup analyses were conducted to examine the variability in treatment effects across different patient characteristics such as age, cancer stage, and the presence of comorbid conditions. All tests were 2-tailed, with a significance level of *P*<.05. To address multiple testing concerns, particularly with numerous secondary outcomes, we used Bonferroni correction or other suitable adjustments to preserve the overall type I error rate. All statistical analyses were conducted using STATA/MP (version 16.0; StataCorp).

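### The article is inconsistent about participants who leave and gives intention-to-treat two different roles, so the 6-month primary result may rest on observed cases only

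*Protocol article*

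**What the plan says.** Three sections of the protocol article bear on participants who leave.

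- **Eligibility Criteria.** After the baseline exclusions comes a separate sentence about participants: "Participants who canceled their pulmonary resection, received a confirmed diagnosis of stage IV lung cancer, or wished to withdraw from the study were excluded". It does not say whether they are excluded from enrolment, from further follow-up or from analysis.
- **Data Collection.** "For participants who discontinued or deviated from the intervention protocols", the article says, "the data collected up to the point of departure were included in the intention-to-treat analysis". The stated purpose is "to maintain the robustness of the trial results and minimize the impact of attrition bias".
- **Statistical Analysis.** "The primary analyses involved independent sample 2-tailed" t tests for continuous variables and chi-square tests for categorical ones, at each follow-up. The same paragraph adds a mixed-model repeated-measures analysis. The next paragraph begins: "In addition to primary analyses, sensitivity analyses probed the robustness of the trial findings". These cover different missing-data assumptions and the effect of adherence, and "This included intention-to-treat and per-protocol analyses".

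The primary outcome is the Mini-MAC at 6 months after resection (T2).

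**The concern.** Read together, the sections leave two things unsettled. The first is whether someone who withdraws after enrolment keeps a place in the analysis: one section appears to remove such people, and another keeps the data of people who depart. The second is the role of ITT. Data Collection presents it as the safeguard for the trial results, but Statistical Analysis places it with per-protocol among the sensitivity analyses, so the safeguard is not attached to the primary comparison.

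This matters more here than in a randomised trial. The cohorts are consecutive and not randomised, and only one has videos, reminders and an extra physician visit. The Limitations section concedes that the program may appeal more to motivated people. It does not say that withdrawal differs by cohort, but differential loss is plausible. If loss is related to adjustment and differs between cohorts, a comparison of those who remain is biased, and a larger sample does not remove that bias.

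**Working it through.** **1. The wording side by side.**

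| Section | Who | What happens |
|---|---|---|
| Eligibility Criteria | Participants with cancelled resection, confirmed stage IV disease, or a wish to leave the study | Excluded; from what is not stated |
| Data Collection | Those who discontinue or deviate from the intervention protocols | Data up to departure kept in ITT |
| Statistical Analysis | All comparisons | t tests among the primary analyses; ITT and per-protocol under sensitivity analyses; mixed model also planned |

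The events in the first row can occur after enrolment, and the sentence stands apart from the baseline exclusions, so it does not read as a screening rule. The first two rows overlap for anyone who leaves both the study and the intervention. They do not coincide for someone who stops the intervention but stays in follow-up.

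**2. What each method does with partial data.** A t test at T2 needs a T2 score. Data at T0 and T1 from someone who leaves before T2 contribute nothing to it, whether or not that person is formally excluded. A mixed model over the repeated measures can use those data. The article does not say which of the two decides the primary question.

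**3. The article's own sample size.** Inputs from Sample Size Calculation and Statistical Analysis: effect size 0.25 (read as a standardised difference), two-sided 0.05, dropout 16%. Power is not stated; 80% is assumed.

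- n per group = 2 × (1.960 + 0.842)² / 0.25² = 251.2, rounded up to 252, as stated.
- 252 / (1 − 0.16) = 300, as stated.

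**4. Power is not the issue.** With the recruited 441 controls and 350 intervention participants (Results), power at 0.25 SD is 93.7%. With 16% missing in each arm, 441 × 0.84 ≈ 370 and 350 × 0.84 = 294 remain, and power is 89.3%.

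**5. Size of a possible bias.** Let d be the share of an arm with no T2 score, and g the amount (in SD) by which its leavers would have scored worse than its stayers.

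- The mean of stayers exceeds the full-arm mean by d × g.
- Bias in favour of LC3P = d(intervention) × g(intervention) − d(control) × g(control).
- SE = √(1/370.44 + 1/294) = 0.078 SD.

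The 16% is the article's planned dropout. The values of g are assumptions; the article gives none.

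| d (both arms) | g intervention | g control | Bias (SD) | Bias / SE | Two-sided false-positive rate | Share of 0.25 |
|---|---|---|---|---|---|---|
| 0.16 | 0.25 | 0 | 0.04 | 0.51 | 8.1% | 16% |
| 0.16 | 0.50 | 0 | 0.08 | 1.02 | 17.6% | 32% |
| 0.16 | 0.25 or 0.50 | same as intervention | 0 | 0 | 5% | 0 |

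The false-positive rate is P(Z > 1.96 − bias/SE) + P(Z < −1.96 − bias/SE).

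The bias is zero when d × g is equal in the two arms. An equal g alone is not enough: with 20% missing in the intervention arm, 12% in the control arm and g = 0.5 in both, the bias is (0.20 − 0.12) × 0.5 = 0.04 SD.

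**The case against.** The best defence is that the sections can coexist. One speaks of leaving the study, the other of leaving the intervention. Under an eligibility heading, being excluded may mean only that participation ended; analysis is not mentioned there. This stands in part: a strict contradiction is not shown. But the Data Collection sentence speaks of departure and attrition, which describes people whose follow-up stops, so the overlap is real and the reader cannot tell who is analysed.

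A reader might infer that the primary result necessarily becomes a completer comparison. The documents do not support that. The mixed model appears in the same paragraph as the primary analyses and can use T0 and T1 data, and sensitivity analyses under different missing-data assumptions are planned. The wording permits an observed-case primary result, and the t test alone would produce one, but the article does not fix that outcome.

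A reader might also attribute the whole bias in the table to the exclusion sentence. That is not right either. The figures describe missing T2 scores, and deleting the sentence would not bring those scores back. Nor need all of the 16% be withdrawals, since the article does not split dropout by reason.

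Finally, detailed analysis sets are commonly left to a full protocol or SAP, so their absence here is no fault. What remains is what the article does state: ITT has one role in Data Collection and another in Statistical Analysis.

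**Conclusion.** The point holds as an inconsistency that should be fixed, not as a demonstrated error in the result. The status of people who withdraw is unclear, and the conflict on that is probable rather than strict. The two roles given to ITT are a plain mismatch. If the t test decides the primary question, the 6-month result is an observed-case comparison and the promised retention of partial data does not protect it.

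Under the one-sided selection assumed above, the bias is 0.04 to 0.08 SD, about a sixth to a third of the 0.25 design effect, with a false-positive rate of about 8% to 18%. These are illustrations resting on assumed leaver–stayer differences, with 16% missing in each arm. The bias is zero if dropout share times leaver–stayer difference is equal in both arms.

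**What to change.** Reconcile the three sections as follows.

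- State that withdrawal ends further participation but does not remove data already collected, where consent allows. The article does not say what participants agreed to on this, so the consent form must be checked.
- Define the primary set as all enrolled participants who underwent resection and were not found to have stage IV disease, analysed in the cohort in which they were recruited. Call it modified ITT, because it still drops some enrolled people.
- Make the T2 contrast from the mixed model, adjusted for baseline, the single primary analysis. Make the t test and the per-protocol analysis supplementary.
- Report post-enrolment exclusions and withdrawals by cohort and reason. The first video is sent at enrolment, so cancelled resections in the intervention cohort come after first exposure and should be visible in these counts.

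The cost is a wording change in the protocol and SAP, with no new data collection. The article says that analyses await completion of the study; on that statement the change can still precede them. The downside is that the mixed model relies on data being missing at random given T0 and T1. It helps only as far as those scores predict the missing T2 values, so the planned missing-data sensitivity analyses should be kept.

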### Intervention

#### Developing the Intervention

The LC^3^P was developed following an extensive literature review [17,21,22], qualitative interviews [19], and cross-sectional studies [15]. These studies aimed to define the informational necessities and challenges faced by lung cancer survivors during their treatment journey. We discovered that the survivors adjusted their postcancer lives by reconciling their expectations with reality [19]. Physical symptoms, psychological challenges, and concerns regarding exercise and nutrition were also examined. Therefore, our intervention delivered timely and stage-specific information from the onset of treatment, primarily through educational videos. This format was selected due to its accessibility, patient friendliness, and potential to alleviate the workload of clinicians.

#### Content of the Intervention

The LC^3^P is a 2-part intervention. The first part of the program comprised 7 educational videos, 4 of which were designed to meet the specific needs of lung cancer survivors. The first video provided general information regarding lung cancer, treatment options, and postsurgery challenges such as pain, emphasizing the importance of smoking cessation and exercise. The second video covered postoperative recovery, addressed symptoms such as reduced lung function and fatigue and offered management strategies. The third video was an exercise tutorial for patients, and the fourth video offered nutritional guidance through a sample meal plan. The latter 3 videos provided general information regarding distress management, return to work [23], and fear of cancer recurrence. The second part of the program was the first postsurgical follow-up with a family medicine physician who assessed the patient’s unique needs using a study-specific checklist (Figure S1 in Multimedia Appendix 1). This visit focused on personalized care through counseling, medication management, and referrals to specialists as needed.

#### Delivery of the Intervention

Eligible participants received a brochure containing QR codes linked to educational videos (Figure S2 in Multimedia Appendix 1). We added QR codes for all the videos in a brochure and gave it to participants before surgery so they could preview the videos if they were curious about what to expect and what to work on after surgery. Participants were strongly encouraged to view the first video before surgery. The link to the first video was sent via SMS text message at the time of enrollment to increase patient accessibility. Around the time of discharge, a research assistant visited the intervention group participants to offer them a second copy of the brochure and sent links to each of the 3 videos, reminding them to watch the videos at their convenience. Data on compliance, satisfaction, and feedback on the educational videos were collected during follow-up visits. Measures were taken until the survivors reported watching all 4 videos or at their 1-year follow-up visit.

During the first follow-up visit after discharge, participants in the intervention group were scheduled to visit a family medicine doctor in addition to regular oncology appointments. During their appointment, the participants discussed any physical or psychological difficulties they had experienced after surgery, and the family medicine doctor provided tailored assistance based on the type and depth of their needs. As our intervention was educational, the participants in the intervention group were qualified to receive other concomitant care or additional necessary measures during the study. A flowchart of the study procedure and intervention is shown in Figure 1.

**Figure 1 figure1:**
[figure not shown]
Flowchart of the Lung Cancer Comprehensive Care Program.

#### Control Group

Participants in the control group received routine preoperative and discharge information regarding hospital stay, costs, and postoperative care. They did not have access to educational programs or postoperative educational support.

### Outcomes

#### Primary Outcome Measures

The primary outcome of the study was psychological adjustment for cancer, measured 6 months after pulmonary resection. The Korean version of the Mini-Mental Adjustment to Cancer (Mini-MAC) was used to assess survivors’ psychological adjustments to cancer. The Mini-MAC is a 29-item scale scored on a 4-point Likert scale (1=definitely does not apply to me and 4=definitely applies to me) previously validated in Korea [24,25]. The Korean-validated scale consists of the following 4 dimensions: helpless-hopeless (8 items), anxious preoccupation (8 items), cognitive avoidance (4 items), and positive attitude (9 items). The positive attitude dimension contained items identical to those of fighting spirit and fatality from the original Mini-MAC. The total score is the sum of all dimension scores, with higher scores indicating a stronger use of coping strategies. Permission to use the Mini-MAC was obtained from the International Psycho-Oncology Society on May 19, 2021.

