### Sample Size Calculation

Based on the primary hypothesis that the intervention group would demonstrate a 25% better psychological adjustment to cancer at 6 months after surgery than the control group, initial calculations with an effect size of 0.25 indicated that 252 participants per group would be required. We aimed for a sample size of approximately 300 per group to account for a dropout rate of 16%. However, to increase the robustness of our findings, allow for potential subgroup analyses, and ensure that the study had sufficient power to detect smaller effect sizes, we enrolled 400 participants per group. The sample size significantly exceeded the required number based on our initial estimates, thereby enhancing the statistical power and potential impact on the study's outcomes.

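### The Mini-MAC total, the only summary score defined for the primary outcome, has no defined favourable direction for the hypothesis of better adjustment

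*Protocol article*

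**What the plan says.** The Primary Outcome Measures section of the protocol article fixes the construct and time point: "The primary outcome of the study was psychological adjustment for cancer, measured 6 months after pulmonary resection". The instrument is the Korean Mini-MAC, described as a "29-item scale scored on a 4-point Likert scale (1=definitely does not apply to me and 4=definitely applies to me"). Every item therefore scores higher the more it applies. The four dimensions are "helpless-hopeless (8 items), anxious preoccupation (8 items), cognitive avoidance (4 items), and positive attitude (9 items"). The section then gives one rule for combining them and one reading of the result: "The total score is the sum of all dimension scores, with higher scores indicating a stronger use of coping strategies". It mentions no reverse scoring.

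The hypothesis has a direction. The Introduction expects that "participants receiving the intervention would demonstrate improved adjustment 6 months after surgery". The Sample Size Calculation section assumes that "the intervention group would demonstrate a 25% better psychological adjustment to cancer at 6 months after surgery than the control group" and uses a single effect size of 0.25, giving 252 per group. The Statistical Analysis section uses two-sided tests at the 0.05 level.

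**The concern.** The stated score measures how much coping a patient reports, while the hypothesis is about how well the patient has adjusted. Judged by their names, helpless-hopeless and anxious preoccupation should fall as adjustment improves, and positive attitude should rise. In a plain sum, a point of helplessness counts the same as a point of positive attitude.

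If the scoring rule is followed as written, a group difference in the total cannot be translated into better or worse adjustment. A program that lowers helplessness and raises positive attitude may show little net change. A significant rise could reflect more positive attitude or more anxiety. The single 0.25 effect presumes an outcome with a known better direction, which this score lacks.

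**Working it through.** **Inputs.** Item counts 8, 8, 4 and 9 and item range 1 to 4 come from Primary Outcome Measures. Effect size 0.25, 252 per group and 16% dropout come from Sample Size Calculation. The two-sided 0.05 level comes from Statistical Analysis. Power is not stated.

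**The plan's own figures.** Items: 8 + 8 + 4 + 9 = 29, as stated, so the total runs from 29 to 116. Sample size: 2(1.960 + 0.842)²/0.25² = 251.2, rounded up to 252, which matches at 80% power (inferred from the match; 90% would need 337). Dropout: 252/(1 - 0.16) = 300, as stated. The sample size reproduces and is not the problem.

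**Equal per-item improvement.** Let each helpless-hopeless and anxious-preoccupation item fall by d and each positive-attitude item rise by d:
- avoidance unchanged: -8d - 8d + 9d = -7d
- avoidance items also fall by d: -7d - 4d = -11d
- avoidance items rise by d: -7d + 4d = -3d

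**Unequal improvement.** The sign is not fixed:
- positive attitude alone, +0.5 per item: 9 × 0.5 = +4.5
- helpless-hopeless and anxious preoccupation alone, -0.5 per item: -16 × 0.5 = -8
- no net change when the per-item gain in positive attitude is 16/9 = 1.78 times the per-item fall in the other two (avoidance unchanged)

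**Extremes of the scale.** Leaving avoidance out, the best-adjusted pattern scores 8 + 8 + 36 = 52 and the worst 32 + 32 + 9 = 73. Avoidance adds 4 to 16, giving 56 to 68 against 77 to 89. The ranges do not overlap. These are floor and ceiling patterns that show the geometry of the score, not a likely treatment contrast.

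**Illustration of power (assumed inputs).** Assume each dimension's SD is proportional to its item count (0.6 per item: 4.8, 4.8, 2.4, 5.4), a benefit of 0.25 SD on each of the three directional dimensions, and 252 per group. With independent dimensions the SD of the total is √(4.8² + 4.8² + 2.4² + 5.4²) = 9.0. With avoidance unchanged the shift is 0.25 × (-4.8 - 4.8 + 5.4) = -1.05, a standardised effect of -1.05/9.0 = -0.12.

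| Case | Total: effect | Total: power |
|---|---|---|
| All three improve; avoidance down, same or up; independent or moderately correlated dimensions | -0.05 to -0.18 | about 7% to 54% |
| Only positive attitude improves | +0.14 to +0.15 | about 33% to 39% |
| Only helpless-hopeless and anxious preoccupation improve | -0.24 to -0.27 | about 77% to 85% |

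All three rows describe benefit, yet the sign differs between them.

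**The case against.** The strongest reply has four parts.

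First, the article never says that the total is the primary endpoint; it names adjustment measured by the Mini-MAC and then describes the instrument. This stands as a qualification. The total is nevertheless the only summary score defined, and the trial is sized on one effect for one quantity that can be better.

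Second, this is a condensed article. Reverse scoring or expected directions could appear in the cited validation work, the supplementary figure on hypothesised effects or the full protocol. Silence alone would be no finding. But the article states both a summing rule and a meaning for high scores, and that meaning is not better adjustment. If items were reversed, a high total would no longer mean stronger use of all the strategies.

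Third, a reader might infer that a better-adjusted patient always scores lower, or that the endpoint cannot show an effect. The documents support neither. The total rises when the gain is mainly in positive attitude, and a two-sided test can detect a difference; what is missing is a reading of its sign. Nothing in the article rules out reporting by dimension either.

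Fourth, the article says that positive attitude contains the fatality items of the original instrument and does not establish that these are adaptive. This stands. The -7d figure treats all nine items as rising with adjustment and is one scenario, not an expected effect.

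**Conclusion.** The concern holds in this form: the only summary score defined for the primary outcome adds dimensions of apparently opposite meaning with no stated reversal, so its favourable direction is undefined for the stated hypothesis. Equal per-item improvement d shifts the total by -7d (-3d to -11d with avoidance), and a gain mainly in positive attitude shifts it up. A significant result in either direction could be benefit or harm. This needs correcting before analysis because it affects the interpretation of the primary result.

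The conclusion rests on reading the plain-sum wording literally, on taking the total as the intended primary score, and on the direction implied by the dimension names. The effect sizes and power values for the total depend on assumed SDs and correlations and only illustrate the range.

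**What to change.** Before any outcome analysis, amend the primary outcome definition as follows:
- Do not use the unreversed total as the primary score.
- Name the validated dimension or dimensions that are primary at T2, with directions: lower is better for helpless-hopeless and anxious preoccupation, higher is better for positive attitude.
- If more than one is primary, control alpha across them, for example by Holm.
- Report cognitive avoidance and the total descriptively. A reverse-coded composite may serve as a sensitivity analysis; it should not be primary, because the article describes no such score as validated.

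**Cost.** No new data are needed. The Ethical Considerations section requires outcome changes to be shared with the investigators, the IRB and the registry. Intervention recruitment ended on October 17, 2022, so 6-month data were due around April 2023. The amendment should therefore record that no outcome comparison had been made.

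Alpha would be shared across up to three tests, and the 252 per group applies to each dimension only before adjustment. At Holm's strictest step (0.05/3 = 0.0167), 80% power at effect size 0.25 needs 2(2.394 + 0.842)²/0.25², about 336 per group. The recruited 441 and 350, less the planned 16% dropout, leave about 370 and 294. Then 0.25 × √(370 × 294/664) = 3.20, and 3.20 - 2.394 = 0.81, which gives about 79% power per dimension at that step, if 0.25 is a fair effect for each dimension.
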